### Intervention

About 4 to 8 weeks after surgery [20], patients in the low-dose group will take oral capecitabine after breakfast and dinner at the dose of 1,000 mg/m^2^ bid, and patients in the approved-dose group will receive the dose of 1,250 mg/m^2^ bid. Each treatment cycle consists of 14 days of capecitabine administration and then 7 days of rest.

Colon cancer patients in both groups are supposed to take eight circles of treatment in total (24 weeks) [22]. Eight circles of treatment will also apply to rectal cancer patients who had neoadjuvant radiotherapy (regimen 1 in Fig. 2). For rectal cancer patients without neoadjuvant radiotherapy, we defined high-risk patients who need concomitant radiochemotherapy (RCT) as patients with positive circumferential resection margin (CRM+) or with lymph node metastasis (N+), and they will receive a total of five circles of chemotherapy [13]. The RCT serves as the third circle and lasts about 6 weeks [13]. During the RCT period, the irradiation dose is 45 Gy/25 fractions, and the capecitabine dose is reduced to 800 mg/m^2^ bid [23] (regimen 2 in Fig. 2). According to the toxic events, the dose of capecitabine will be adjusted following the drug instruction of Xeloda® [15]. Any patients who have intolerable toxic or side effects will discontinue the medication.

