### Outcomes

#### Primary outcome

The primary outcome of the LC-ACEC trial is 3-year disease-free survival (DFS), which is calculated from the date of randomization to whichever of the following events occurs first in 3 years: local recurrence, metastasis, death from any causes, or development of other malignances.

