#### Follow-up and data collection

The medical history and physical examination will be taken immediately at the outpatient clinic. After patients pass the selection procedure and sign the informed consent form, a series of investigations, including complete blood test (for example, blood cell count and blood chemistry), tumor markers of carcinoembryonic antigen (CEA) and carbohydrate antigen 19-9 (CA 19-9), total abdominal computed tomography (CT) scan, and chest radiograph, will be scheduled. It is worth mentioning that before every circle of chemotherapy, renal function of each participant will be monitored and evaluated by calculating the creatinine clearance. When participants finish every circle of chemotherapy, investigators will assess the toxic and side effects by using NCI-CTC and record any modification or discontinuation of capecitabine. In view of possible compromised compliance of elderly patients, returned medication will be checked at the clinic, and patients who discontinue the treatment for more than 1 week (except for toxic effects) will be withdrawn from this trial. When the whole treatment is over, patients will come to the hospital for a check-up every 3 months in the first 2 years and every 6 months afterward. Each time, the complete blood test, tumor markers, total abdominal CT scan, chest radiograph, and rectal examination will be conducted to help oncologists verify the possible local recurrence and metastasis, and the QoL questionnaire will be filled. We will follow up patients on a corresponding timeline at the clinic or by phone. All the data of each patient will be recorded in a case report form (CRF) in time.

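### Recurrence scans are timed from the end of treatment but DFS runs from randomization and stops at 3 years, so the last scan that can count moves with each patient's treatment length: a small effect, cheap to remove

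*Protocol article*

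**What the plan says.** Under Primary outcome, DFS is "which is calculated from the date of randomization to whichever of the following events occurs first in 3 years". The origin is randomization, and only events in the first 36 months count.

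Under Follow-up and data collection, the recurrence work-up has another origin: "When the whole treatment is over, patients will come to the hospital for a check-up every 3 months in the first 2 years". After those 2 years the interval lengthens to 6 months. These visits are how recurrence is looked for: abdominal CT, chest radiograph and "rectal examination will be conducted to help oncologists verify the possible local recurrence and metastasis". The article describes no restaging scan during treatment and no assessment tied to 3 years from randomization.

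Under Intervention, planned length is common to the arms: "Colon cancer patients in both groups are supposed to take eight circles of treatment in total (24 weeks"). The regimen for high-risk rectal patients without neoadjuvant radiotherapy has five cycles, of which "The RCT serves as the third circle and lasts about 6 weeks". Treatment may also end early: "Any patients who have intolerable toxic or side effects will discontinue the medication". The follow-up section withdraws patients who interrupt for more than a week, but exempts interruptions for toxicity, so toxicity delays longer than a week can occur.

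**The concern.** A recurrence found only by imaging is dated at the scan that shows it. If the scan calendar starts at the end of treatment and the endpoint closes 36 months after randomization, the length of treatment decides how late in the window a patient is last examined. Treatment length is known only after randomization, and the dose under test may affect it. Completion is itself a key secondary outcome, and the Background gives reasons to expect tolerance to depend on dose.

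If the arms differ in how long treatment actually takes, recurrences could enter or drop out of the primary comparison for reasons unrelated to efficacy. In a non-inferiority trial that matters in either direction: lost control events push the hazard ratio (low dose over approved dose) towards the margin, and lost low-dose events pull it away.

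**Working it through.** **The plan's own figure.** Events = 4 × (1.960 + 0.842)² / (ln 1.30)² = 456.1, which agrees with the stated 456. This point does not question that number.

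**Scan calendar.** Let T be the time from randomization to the end of treatment, in months of 30.4375 days. Scans fall at T + 3, 6, …, 24, then T + 30, T + 36 and so on. A scan counts if it falls at or before month 36.

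| Treatment ends after | T (months) | Last scan that counts | Next scan |
|---|---|---|---|
| 3 weeks | 0.69 | 30.7 | 36.7 |
| 12 weeks | 2.76 | 32.8 | 38.8 |
| 18 weeks (4 × 3 + 6, radiochemotherapy regimen) | 4.14 | 34.1 | 40.1 |
| 24 weeks (eight cycles) | 5.52 | 35.5 | 41.5 |
| 26 weeks | 5.98 | 35.98 | 41.98 |
| 27 weeks | 6.21 | 30.2 | 36.2 |

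The step occurs when T + 30 passes 36, that is at T = 6 months: 6 × 30.4375 / 7 = 26.1 weeks. A patient on the planned 24 weeks has about 2 weeks of slack if dosing starts on the day of randomization. Any lag before the first dose uses up that slack. The article times the start of treatment from surgery, so the lag is not given.

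**Size.** Inputs from the article: 60 % 3-year DFS, hence a constant hazard of −ln(0.60)/36 = 0.0142 per month. Assumptions, none of them in the article:
- true hazard ratio 1.00;
- 80 % of the hazard is recurrence found at the next scheduled scan, and the rest is dated exactly;
- overruns of about 2 to 6 weeks in 40 % (approved dose) v 15 % (low dose) of completers;
- early stopping in 30 % v 5 %, spread evenly over cycles 1 to 7;
- scan clock starting at the actual end of treatment.

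Simulated hazard ratio, low over approved dose, with DFS cut at 36 months:

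| Scenario | No start lag | Lag of 4 weeks |
|---|---|---|
| Overruns only | 1.02 to 1.03 | about 1.00 |
| Early stopping only | about 1.00 | about 0.98 |
| Both | about 1.02 | about 0.98 |

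With no lag, overruns on the approved dose lose control events and raise the ratio. With a 4-week lag, completers in both arms are already past the step. Early stoppers then keep a later countable scan, so the arm with more of them records more events. Swapping the overrun rates between arms, with no lag, gives about 0.97. Scans timed from randomization give 1.00.

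**Longer follow-up.** 926 patients at 60 % 3-year DFS give at most 0.40 × 926 = 370 events within 3 years, so 456 cannot be reached under the cut. With 10 % drop-out, 456 events need an event probability of 456 / (926 × 0.9) = 0.547, or −ln(1 − 0.547)/0.0142 = about 56 months. With a 56-month cut the simulated ratio is about 1.00 in every scenario.

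**The case against.** The strongest reply is that the article plans identical treatment in both arms. The 24- v 18-week difference is by regimen, and stratification by stage and site should largely balance it. That stands. A reader might infer that treatment length differs by arm, but the article does not say so. It gives only reasons why it could. The 51 % dose-reduction figure, and the 95 % v 70 % completion without reduction (from a non-randomized breast cancer comparison), concern dose, not duration.

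The overrun rates are also assumed, and the answer depends on the unstated start lag. At zero lag, ordinary visit scatter (standard deviation 2 weeks, assumed) brings the overrun effect down to between 1.01 and 1.02. Deaths, and recurrences that come to light between visits, do not wait for the calendar, and the article allows contact by phone. All of this limits the size. It does not reconcile the two clocks.

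Visit windows, and the rule for an early stopper's calendar, may well be in the full protocol, and their absence here is not criticised. The anchor itself is stated in the article, and it does not fit the stated endpoint.

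Two stronger readings should be resisted. One is a loss of power: that would pair a 36-month cut with 456 events, which this design cannot supply, so no power figure is warranted. The other is a large bias. Ratios of 1.14 to 1.15 arise only if every approved-arm completer finishes 3 weeks late and every event is found by scan. With a 4-week lag the same scenario gives 0.96. Nothing in the article supports such a uniform delay.

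**Conclusion.** The mismatch is real and can be read directly from the text. For an individual, the last scan that can count moves between about month 30 and month 36 with treatment length. A between-arm effect is a possibility, not a stated fact, and its sign cannot be predicted. Under the assumptions above, with overruns and early stopping commoner on the approved dose and a start lag of 0 to 4 weeks, a true hazard ratio of 1.00 would appear as about 0.98 to 1.03, against a margin of 1.30. This holds if DFS is cut at 3 years as the outcome definition says. If follow-up runs on well past 3 years, the effect is negligible. It is a worthwhile, inexpensive improvement and not a threat to the trial.

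**What to change.** In Follow-up and data collection, time disease assessments from randomization, identically in both arms and all regimens, and state that the dates do not move when treatment is delayed, shortened or stopped. Keep about the present spacing and include one assessment at month 36, for example months 6, 9, …, 30 and then 36. That is ten scans within 3 years, against nine now for a patient finishing at 24 weeks. The 456 events and 926 patients are unaffected.

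The cost is protocol wording and a revised visit calendar. A patient with delayed treatment may be scanned close to, or before, the last cycle. A patient who stops very early would have the first scheduled scan at a fixed date instead of 3 months after stopping.

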### Randomization and blinding

All participants fulfilling the inclusion criteria will be randomly allocated into either the low-dose or the approved-dose group. We use a computer-generated blocked randomization sequence with the block size of four according to the previous published trial conducted in WCH [21]. Patients are randomly assigned by stratification of disease stage (stage II or III) and primary tumor site (colon or rectum). To achieve allocation concealment, opaque envelopes with sequential numbers are adopted to seal the assignment and are accessible only for investigators not involved with this trial. After enrollment of each patient, the envelope is sent to an independent investigator, who is not involved in patient evaluation, to assign participants to either the low-dose or the approved-dose group. This is an open-label trial; thus, patients, investigators, and data analysts are aware of the group assignment.

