#### Sample size and statistics

The LC-ACEC trial aims to identify the non-inferiority of 3-year DFS of patients in the low-dose capecitabine adjuvant chemotherapy group versus the approved-dose group. We assumed that a background 3-year DFS was 60 % and predefined the non-inferiority margin of the hazard ratio (HR) as 1.30. When 456 events of the primary endpoint 3-year DFS occur, the efficacy analysis will be conducted. We chose a statistical power of 0.80 and a significance level of 0.05 (two-sided). Given the 10 % drop-out for elderly patients, the calculation yielded a sample size of 926 patients (463 in each arm) [11, 25].

The intention-to-treat analysis will be applied with all patients who undergo randomization in this trial. With regard to survival data, HRs with 95 % confidence intervals (CIs) will be presented by Kaplan-Meier survival estimates. Additionally, Cox proportional HRs with 95 % CIs will be calculated on the basis of subgroups of different characteristics (that is, age, sex, stratum, and Charlson comorbidity index), which can identify the influence of competing risk factors for the outcome event. For the primary outcome of 3-year DFS, the non-inferiority will be concluded if the upper limit of the 95 % CI is not more than 1.30 (predefined non-inferiority margin). As for other outcomes, proportions will be compared by using chi-squared test, and continuous data will be analyzed by *t* test. All the statistical analyses will be conducted by using SPSS version 20 software (SPSS, Inc., Chicago, IL, USA).

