It is worth mentioning that our trial still has limitations. The blinding is limited by the open-label nature of the trial. In addition, time of follow-up is relatively short to achieve long-term outcome given the loss rate caused by high population mobility in this region. Moreover, our trial includes only Chinese patients and this to some degree limits the applicability to other ethnicities because of inter-ethnic differences in tolerance for capecitabine. In summary, the LC-ACEC trial is the first randomized controlled trial to investigate the efficacy and safety of the low-dose capecitabine adjuvant chemotherapy (1,000 mg/m^2^ bid) in elderly patients with stage II/III CRC. If non-inferiority of the low-dose strategy is verified, this can be recommended as a new standard capecitabine adjuvant chemotherapy strategy, specifically for the large group of elderly patients with stage II/III CRC, and this is not only cost-effective but also beneficial for their QoL. The result of this trial will provide evidence on a more specific adjuvant chemotherapy strategy for elderly patients with stage II/III CRC.

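### Recurrence and metastasis, the judged components of the primary endpoint, are verified by oncologists in a trial where investigators know the arm, and no arm-blind step is described

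*Protocol article*

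**What the plan says.** The primary outcome is DFS within 3 years of randomization, ended by the first of "local recurrence, metastasis, death from any causes, or development of other malignances" (Protocol article, Primary outcome). After treatment, patients attend "a check-up every 3 months in the first 2 years and every 6 months afterward", with the same tests in both arms. At each visit the markers, abdominal CT, chest radiograph and "rectal examination will be conducted to help oncologists verify the possible local recurrence and metastasis" (Follow-up and data collection).

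On masking, Randomization and blinding states: "This is an open-label trial; thus, patients, investigators, and data analysts are aware of the group assignment". The one independent person described there is someone "who is not involved in patient evaluation, to assign participants to either the low-dose or the approved-dose group", so that role ends at allocation. The monitoring board reviews trial data, including adverse events and drop-outs; confirming recurrence is not among its listed tasks (Safety and data monitoring). The Discussion concedes that "The blinding is limited by the open-label nature of the trial" and offers no countermeasure.

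The authors "predefined the non-inferiority margin of the hazard ratio (HR) as 1.30", and non-inferiority is concluded from the upper 95% confidence limit against that value (Sample size and statistics).

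**The concern.** Patients and prescribers cannot easily be masked to two capecitabine doses. It does not follow that the people who decide whether and when a recurrence has occurred must know the dose, yet the protocol presents their knowledge as a consequence of open-label treatment.

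Two of the four endpoint components, local recurrence and metastasis, involve judgement. A clinician who knows the arm may be quicker to suspect failure on the lower dose, or more willing to wait because the doses are expected to be equivalent. The first works against the non-inferiority claim and the second works towards it. Masking the analysts would not help, because the event and its date would already have been recorded. The whole conclusion rests on one hazard ratio compared with 1.30, so a small arm-dependent shift matters.

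**Working it through.** **Inputs from the protocol** (Sample size and statistics): margin 1.30; two-sided 0.05, that is 0.025 for the bound that decides; power 0.80; 456 events; 3-year DFS 60%; 463 patients per arm; 10% drop-out.

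**The plan's own figure.** Schoenfeld's formula with true HR 1 gives 4 × (1.960 + 0.842)² / (ln 1.30)² = 456.1, which reproduces the 456.

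**Events available under a strict 3-year cut-off.**
- HR 1.0 with 10% of patients lost: 926 × 0.9 × 0.40 = 333. With none lost: 926 × 0.40 = 370.
- HR 1.30, none lost: 463 × 0.40 + 463 × (1 − 0.60^1.3) = 185.2 + 463 × 0.485 = 410. With 10% lost: 369.

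The illustration uses 333 to 410 events. It does not use 456, because that number needs events after 3 years to count, and then deferral past 3 years would lose nothing.

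**False-claim risk if a share m of low-dose events is lost, with none lost in the other arm** (m is assumed). The observed HR is 1.30 × (1 − m), and the risk is Φ(−1.96 + ln[1/(1 − m)] × √D / 2). √D / 2 is 9.12 for D = 333 and 10.12 for D = 410.
- m = 0: 2.5%.
- m = 3%: HR 1.261; shift 0.0305 × 9.12 to 10.12 = 0.28 to 0.31; risk 4.6 to 4.9%.
- m = 5%: HR 1.235; shift 0.0513 × 9.12 to 10.12 = 0.47 to 0.52; risk 6.8 to 7.5%.

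**If only recurrences can be lost.** Deaths cannot be deferred. Suppose recurrences are 70% of events (assumed).
- 3% of recurrences lost: m = 0.021; shift 0.0212 × 9.12 to 10.12 = 0.19 to 0.21; risk 3.9 to 4.1%.
- 5% of recurrences lost: m = 0.035; shift 0.0356 × 9.12 to 10.12 = 0.32 to 0.36; risk 5.1 to 5.5%.

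**Opposite bias.** Suppose the true HR is 1.0 and 5% more low-dose events are called (assumed), so the observed HR is 1.05. Power is Φ(ln[1.30/HR] × √D / 2 − 1.96). With 333 to 370 events it falls from 67 to 71% to about 50 to 54%.

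**What a one-visit deferral can remove.** With constant hazard (assumed), the last 6 months hold (0.653 − 0.600)/0.400 = 13% of 3-year events at 60% DFS. At HR 1.30 the share is (0.575 − 0.515)/0.485 = 12%. Losing 5% of all low-dose events by deferral alone would therefore mean deferring about 38 to 40% of the events in that interval (0.05/0.133 to 0.05/0.124). Losing 3% would mean deferring 23 to 24%.

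**The case against.** The best case for the plan has four parts.

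1. **Detection is partly protected.** Visits and tests are the same in both arms, so scheduled ascertainment does not depend on suspicion, and death from any cause is not open to this bias. This stands and limits the size. It protects how often patients are examined, not how an equivocal finding is called.

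2. **Deferral mostly changes the date.** A lesion left open is looked at again 3 or 6 months later, and a recurrence that proves fatal within the window counts anyway. This stands too. The 5% case needs heavy deferral near the cut-off, or some events never called, and should be read as an upper illustration.

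3. **A journal article condenses.** Details of imaging requests and endpoint review may sit in the full protocol. However, the article goes beyond silence: it says who knows the arm, down to the analysts, and who verifies recurrence. That is a stated way of calling events.

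4. **The remedy is incomplete.** It moves the judgement to the reporting radiologist, unscheduled scans are still triggered by unmasked clinicians, and events learned by phone may have no report. This is correct and is why a fallback rule is needed.

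A reader might also infer more than the documents support. They give no split of DFS events by type, and at ages 70 to 90 deaths from other causes and second cancers may be a large share, so recurrence cannot be called the main component. They do not say who reports the scans or whether requests show the arm, so it cannot be said that scans are read with knowledge of it. That the verifying oncologists know the arm is a strong inference from the statement about investigators, who are not further specified. Cost is not addressed, so a fix at no cost cannot be claimed.

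**Conclusion.** The point holds as a design weakness that is cheap to reduce. The judged components of the primary endpoint are verified by oncologists in a trial whose investigators and analysts are stated to know the arm, with no arm-blind step described and only an acknowledgement of the limitation.

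The size is illustrative. A loss of 3 to 5% of low-dose DFS events, in that arm only, would raise the false-claim risk from 2.5% to about 4.6 to 7.5% at a true HR of 1.30. If the same percentages apply to recurrences alone and these are 70% of events, the range is about 3.9 to 5.5%. The loss rates, their one-sidedness and the 70% are assumptions, and nothing in the documents shows that such bias will occur or in which direction. The Discussion itself raises the worry that a lower dose might compromise efficacy, which could equally push calling against the low-dose arm and cost power. The 456 events and 926 patients are unaffected by this point.

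**What to change.** Add to the protocol and the imaging request form:

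- The dose arm is left off the scheduled CT and chest-radiograph requests, so that they are reported without it.
- The recurrence or metastasis event and its date come from the first routine radiology or pathology report that documents it.
- Every unscheduled scan is logged with its trigger, so that its frequency can be compared between arms.
- One fallback dating rule, the same for both arms, covers equivocal reports and recurrences known only clinically or by phone.

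The cost is small: some rule-writing and a change to the request form, with no added central reader and no change in sample size. Some events will be dated by the fallback, and unscheduled scans will still be triggered by clinicians who know the arm, so the bias is reduced but not removed. If the full protocol already has requests without the arm, a sentence saying so settles that part.

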## Methods

### Study objective

The primary objective of the LC-ACEC (Low-dose Capecitabine Adjuvant Chemotherapy for Elderly Patients With Stage II/III Colorectal Cancer) trial is to investigate the non-inferiority of the efficacy of low-dose capecitabine (1,000 mg/m^2^ bid) applied in adjuvant mono-chemotherapy for elderly patients with stage II/III CRC. Furthermore, we aim to compare the toxic and side effects, completion rate, and quality of life (QoL) of the low-dose strategy with the approved-dose strategy (1,250 mg/m^2^ bid).

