#### Secondary outcome

Several secondary outcomes are adopted in this trial. In addition to the primary outcome of 3-year DFS, the 3-year overall survival is calculated from the randomization to the date of death from any causes. Toxic and side effects during adjuvant chemotherapy will be closely observed and evaluated by using National Cancer Institute Common Toxicity Criteria (NCI-CTC) version 2.0. Based on the toxic and side effects, we will keep every record of modification or discontinuance of capecitabine and calculate the completion rate of the treatment as one of the key secondary outcomes. Moreover, QoL data are recorded by using a Chinese translation of European Organisation for Research and Treatment of Cancer Core QoL Questionnaire C30 (EORTC QLQ-C30) [24].

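### The only stated quality-of-life time points fall after treatment ends, so the planned dose comparison of quality of life cannot speak to the treatment period

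*Protocol article*

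**What the plan says.** The Study objective section makes QoL one of three comparisons beside the primary outcome: "we aim to compare the toxic and side effects, completion rate, and quality of life (QoL) of the low-dose strategy with the approved-dose strategy". The Secondary outcome section names the instrument and gives no time points: "QoL data are recorded by using a Chinese translation of European Organisation for Research and Treatment of Cancer Core QoL Questionnaire C30".

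Timing appears only under Follow-up and data collection, which describes three phases:

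- **After consent, before treatment:** "a series of investigations, including complete blood test (for example, blood cell count and blood chemistry), tumor markers of carcinoembryonic antigen (CEA" and CA 19-9, followed by an abdominal CT scan and a chest radiograph.
- **During treatment:** "before every circle of chemotherapy, renal function of each participant will be monitored and evaluated by calculating the creatinine clearance". After each cycle, investigators grade toxicity by NCI-CTC and record any change or stopping of capecitabine. Returned medication is also checked.
- **After treatment:** "When the whole treatment is over, patients will come to the hospital for a check-up every 3 months in the first 2 years", then every 6 months. The questionnaire belongs to these visits, whose tests are done "to help oncologists verify the possible local recurrence and metastasis, and the QoL questionnaire will be filled".

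Under Sample size and statistics, the only line that would apply to a QoL score is that "continuous data will be analyzed by *t* test". The Discussion says QoL is impaired by the toxic effects of chemotherapy. It adds that, if the low dose is shown to be non-inferior, "this is not only cost-effective but also beneficial for their QoL".

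**The concern.** The argument for a lower dose is better tolerability. The Discussion's own mechanism runs from dose to toxicity to QoL, and that mechanism acts mainly while patients take the drug. The plan follows toxicity cycle by cycle but places the QoL questionnaire only after the difference in exposure has ended.

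A null QoL result from such data could mean that dose makes no difference, or that a difference existed during the cycles and had faded before anyone was asked. A positive result would describe recovery after chemotherapy, not the experience of receiving it. Neither would settle whether the lower dose is easier to live with during treatment. Data not collected during treatment cannot be recovered later, and the Trial status section says that recruitment is under way.

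**Working it through.** **Inputs (Intervention; Follow-up and data collection).** A cycle is 14 days of drug plus 7 days of rest, or 21 days. Regimen 1 has eight cycles, stated as 24 weeks. Regimen 2 has five cycles, the third being radiochemotherapy of about 6 weeks. Check-ups after treatment are 3-monthly (about 13 weeks) at first. The date of the first check-up is not given.

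**Step 1: length of treatment.**
- Regimen 1: 8 × 21 days = 168 days = 24 weeks, which reproduces the stated figure.
- Regimen 2: 4 × 3 weeks + about 6 weeks = about 18 weeks. One capecitabine dose is stated for the radiochemotherapy block, so the assigned doses differ over the other four cycles (4 × 3 = 12 weeks).

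**Step 2: QoL scores scheduled in that time.** Going through the three phases, the questionnaire is named at none of the pre-treatment, pre-cycle or post-cycle assessments. The number of stated on-treatment scores is 0 in both regimens.

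**Step 3: week of the first score, counted from the start of treatment.**

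| | First check-up at end of treatment | First check-up 3 months later |
|---|---|---|
| Regimen 1 | week 24 | 24 + 13 = week 37 |
| Regimen 2 | week 18 | 18 + 13 = week 31 |

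None of the four readings places a score within the cycles.

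**Step 4: what late measurement could cost (illustration only).** Assume an on-treatment difference of 0.3 SD, of which a fraction f persists to the post-treatment visit. Assume also 417 patients analysed per arm, from 926 × 0.9 / 2 = 416.7. The documents give neither 0.3 nor f. Two-sided 0.05 power is Φ(0.3f / √(2/417) − 1.96), with √(2/417) = 0.0693:
- measured on treatment (f = 1): Φ(4.33 − 1.96) = 99%
- f = 0.50: Φ(2.17 − 1.96) = 58%
- f = 0.25: Φ(1.08 − 1.96) = 19%
- f = 0.10: Φ(0.43 − 1.96) = 6%

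**Step 5: value of a baseline score.** Adjustment multiplies the variance of the comparison by 1 − r², where r is the correlation of the baseline score with the later one. The documents do not give r. For assumed values of 0.3, 0.5 and 0.7 the factor is 0.91, 0.75 and 0.51, a reduction of 9%, 25% and 49%.

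**The case against.** The strongest reply is that a journal article condenses a fuller protocol. The list of pre-treatment investigations is worded as non-exhaustive, and the Secondary outcome section does not confine QoL to any period, so an unreported baseline or on-treatment questionnaire cannot be excluded. This stands, most clearly for the baseline. It is weaker for the treatment period: the article itemises the per-cycle assessments down to creatinine clearance and returned medication, and assigns the questionnaire explicitly to one phase. That is a stated timing, not merely a missing detail.

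A second reply is that on-treatment tolerability is already captured every cycle through toxicity grades, dose changes and the completion rate, which the article singles out as a key secondary outcome. That limits the importance of the point. It does not supply the patient-reported comparison that the objective promises.

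Several stronger readings are tempting, and the documents do not support them:

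- **That the trial announces a QoL gain during chemotherapy.** The Discussion says only that the low dose would benefit QoL and names no period. The link to the treatment period is an inference from the toxicity mechanism described there.
- **That the first score necessarily comes at week 37, when acute toxicity has resolved.** The first check-up is undated, and the documents say nothing about how quickly toxicity resolves.
- **That the lack of a baseline makes the QoL comparison biased.** Randomization supports an unadjusted post-treatment comparison among those assessed. The loss is in precision and in change scores.
- **That the t test is an error.** The sentence is a general one for continuous outcomes, and the detailed QoL model may properly sit in an analysis plan that is not shown.

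**Conclusion.** The point holds for the schedule as the article states it. QoL is a comparative objective, yet no score is scheduled during the 24 weeks of regimen 1 or the roughly 18 weeks of regimen 2. The QoL comparison, and the Discussion's statement of benefit, therefore cannot speak to the treatment period. This conclusion needs no assumption about when the first check-up falls, because every reading puts it at or after the end of treatment.

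The power figures are illustrative and depend on an assumed 0.3 SD difference and assumed persistence. The precision gain of 9–49% depends on an assumed r of 0.3 to 0.7. The missing on-treatment score is the main gap and the missing baseline is secondary. Disease-free survival, the sample size and the toxicity outcomes are not affected. If the full protocol does schedule earlier questionnaires, a one-line clarification closes the point.

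**What to change.** 1. Schedule the QLQ-C30 before randomization and at end-of-cycle assessments that already take place, for example every second cycle, and keep it at follow-up. Every second cycle means cycles 2, 4, 6 and 8 in regimen 1 and cycles 2 and 4 in regimen 2. Use the same point within the cycle in both arms.
2. Compare on-treatment QoL between arms, adjusting for baseline where it is available, and report post-treatment QoL separately.
3. Date the first post-treatment check-up.
4. For patients whose on-treatment data have already been missed, limit the QoL conclusion to the post-treatment period and word the expected benefit accordingly.

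On that example schedule the cost is one baseline form plus four (regimen 1) or two (regimen 2) further questionnaires per patient, with case report form pages and a short protocol amendment. No new visits are needed and the sample size does not change. The downsides are a small added burden on elderly patients and no baseline score for those already enrolled.
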